### Baseline data

Baseline assessment includes demographics, hobbies, sports, work status, smoking status, neck and arm pain history of patient and family, medical history and co-morbidity, body mass index, and neurological signs and symptoms. The patient's satisfaction at work will be registered. The treatment preference of patient, surgeon and research nurse will also be assessed.

### Outcome assessment

We will assess the below described validated outcome parameters. Patients will not be informed about their previous scores. Follow-up examination will take place at 8, 26, 52, 104 and 260 weeks after randomisation. Patients will be neurologically examined and questionnaires will be filled in. At 2, 4, 12, 156 and 208 weeks after randomisation, questionnaires will be sent by mail (Table 2).

**Table 2 T2:** Data collection and outcome measures.

	Intake surgeon	Intake research nurse	Informed consent	Surgery	Follow-up 2 weeks	Follow-up 4 weeks	Follow-up 8 weeks	Follow-up 12 weeks	Follow-up 26 weeks	Follow-up 52 weeks	Follow-up 104 weeks	Follow-up 156 weeks	Follow-up 208 weeks	Follow-up 260 weeks
Visit	1	2	3	4			5		6	7	8			9
Inclusion/exclusion criteria	X													
Informed consent			X											
Treatment preference	X	X												
Expected recovery	X	X												
Demographics & diagnosis	X	X												
Basic physical examination	X													
Neurological examination	X	X					X			X	X	X	X	X
Randomisation				X										
Dynamic X-ray	X						X			X	X	X	X	X
MRI	X										X			X
CT	X										X			X
NDI		X			X	X	X	X	X	X	X	X	X	X
McGill		X			X	X	X	X	X	X	X	X	X	X
VAS arm and neck		X			X	X	X	X	X	X	X	X	X	X
SF-36		X			X	X	X	X	X	X	X	X	X	X
HADS		X					X		X	X	X	X	X	X
Karasek		X			X	X	X	X	X	X	X	X	X	X
Likert					X	X	X	X	X	X	X	X	X	X
Macnab							X		X	X	X			X
EuroQol and VAS		X			X	X	X	X	X	X	X	X	X	X
Cost diaries								X	X	X	X	X	X	X
Complications				X			X			X	X	X	X	X
Re-operation							X			X	X	X	X	X

### Primary outcome measure

*Accelerated adjacent disc degeneration (AADD). *Although the evaluation of cervical disc degeneration is very important in this clinical setting, there is no established standardized nomenclature. Radiographic degenerative changes at the superior and inferior adjacent levels will be recorded by means of X-ray at intake and each follow-up moment. At 2 and 5 years follow-up both CT and MRI of the cervical spine will be performed. In this trial we will use a recently developed MRI-based grading system for cervical intervertebral disc degeneration, which has been shown reliable[21](Table 3) It is of uppermost importance that radiological adjacent level disease will be accompanied by concomitant complaints, but we will evaluate radiographic adjacent level disease without symptoms as well.

**Table 3 T3:** MRI-based grading system for cervical intervertebral disc degeneration.

Grade	Nucleus signal intensity	Nucleus structure	Distinction of nucleus and annulus	Disc height
I	Hyperintense	Homogenous, white	Clear	Normal
II	Hyperintense	Inhomogenous with horizontal band, white	Clear	Normal
III	Intermediate	Inhomogenous, grey to black	Unclear	Normal to decreased
IV	Hypointense	Inhomogenous, grey to black	Lost	Normal to decreased
V	Hypointense	Inhomogenous, grey to black	Lost	Collapsed

### Secondary outcome measures

### 1) Neck Disability Index (NDI)

The NDI is a 10-item questionnaire on 3 different aspects; pain intensity, daily work related activities and non-work related activities. Each item is scored from 0 to 5 and the total score ranges from 0 (best score) to 50 (worst score). The NDI is a modification of the Oswestry Low Back Pain Index and has been shown to be reliable and valid for patients with cervical pathology[22-24].

### 2) Short-Form 36 (SF-36)

This is a generic health status questionnaire that can easily be filled out at home. The questionnaire consists of 36 items on physical and social status of the patient subdivided in 8 domains; 1) physical functioning, 2) physical restrictions, 3) emotional restrictions, 4) social functioning, 5) somatic pain, 6) general mental health, 7) vitality and 8) general health perception. The questions are scored on a scale of 0 (worst health) to 100 (ideal health). This questionnaire has been used frequently and is validated in surgical studies on spinal column pathology[25-27].

### 3) Pain

Pain intensity, measured by Visual Analogue Score (VAS) of arm and neck and McGill pain Questionnaire is chosen as secondary outcome measure.

#### VAS arm pain

This parameter will measure the experienced pain intensity in the arm during the week before visiting the research nurse. Pain will be assessed on a horizontal 100 mm scale varying from 0 mm (no pain) to 100 mm (worst pain imaginable). Patients do not see the results of earlier assessments and will score the pain experienced at the visit. Reliability, validity and responsiveness of VAS have been shown[28].

#### VAS neck pain

Since many patients with radicular arm pain have neck pain as well, we will also measure the intensity of neck pain.

#### McGill Pain Questionnaire

The McGill Pain score consists of 4 parts: 1) quality and intensity of pain, 2) effects of pain on daily activities, 3) VAS, and 4) distribution and course of pain. The McGill pain score is shown to be highly effective to evaluate the effects of treatment on pain[29]. The Dutch version of McGill pain score will be used in this study[30].

### 4) Karasek Job Content Questionnaire

The Job Content Questionnaire is developed by Karasek to measure the on-the-job impact of chronic health problems and/or treatment[31]. We will use the Dutch version of the Karasek which has been shown reliability and validity[32].

### 5) Hospital Anxiety Depression Scale (HADS)

The HADS is a self-assessment scale which is developed to detect anxiety and depression in patients attending a medical clinician and has been shown reliable and valid[33]. The HADS consists of a 7-item depression scale and a 7-item anxiety scale. The score ranges from 0-21 with a high score being indicative for depression/anxiety.

### 7) Perceived recovery

This is a 7-point Likert scale measuring the perceived recovery, varying from "complete recovery" to "worse than ever". This outcome scale has been used in previous studies and is regarded valid and responsive to change[34]. Complete recovery and almost complete recovery are defined as good result. Next to this global self-assessment, a job and hobby specific Likert will be scored. During the intake of the study the patient will be asked to rank their 5 most important functional disabilities in daily life, which they can use in their own evaluation overall and in separate items. Moreover, the expected recovery from both patient, surgeon and research nurse will be evaluated.

### 8) Utility measurements

The EuroQol (EQ-5D) measures 5 dimensions (mobility, self-care, daily activities, pain/discomfort, anxiety/depression), on a 3 point scale (no, some, or extreme problems). For each health state described by the patients, a utility score can be calculated that reflects society's valuation of that health state. The Dutch tariff for the EQ-5D will be used[35]. Similarly, SF-6D utilities will be calculated from the SF-36 profiles[36]. Whereas the EQ-5D and SF-6D provide society's assessment of the patients' health, the patients themselves will also assess their own health on VAS, ranging from 0.0 (as bad as death) to 1.0 (optimal health). Both the EQ-5D and the VAS will be reported in questionnaires filled out at home.

### Other outcome measures

### 1) Costs

The direct medical costs of hospital admission (fixed costs per admission, and variable costs per admission day) and surgery (including personnel and implants) will be estimated in all participating hospitals for cost-analysis. Using cost diaries, the patients will register other medical care (including physiotherapy, visits to general practitioners and medical specialists, nursing care, and medication) and non-medical costs (including out-of-pocket expenses, domestic help, and absenteeism). Each diary will cover 3 months and the research nurse will go through the diary with the patient on every follow-up visit, throughout the study period of 2 years. Costs will be calculated using standard prices, including time and travel costs [37].

To estimate the indirect costs, like productivity costs, patients will register absenteeism in the diary and the research nurse will register the patient's work situation, work efficiency, and gross income on follow-up moments. Absenteeism will be valued to the friction-cost method.

### 2) Incidence of re-operations

In previous studies concerning spine surgery the incidence of re-operations has been used to assess outcome. Also in this study, we will assess the incidence of re-operation. Every surgical re-exploration in both groups will be considered as re-operation.

### 3) Complications

A systematic assessment of complications (including wound infection, deep venous thrombosis, urine tract infection, haematoma, progressive neurological deficit, dysphagia, and hoarseness) will be carried out by the surgeon and research nurse. Surgeons will also document perioperative complications like cerebrospinal fluid leakage, vascular injury, nerve root damage, and malposition of the implant.

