### Intervention

Patients will be randomised into anterior discectomy *sec *(group A), anterior discectomy with interbody fusion (group B), and anterior discectomy with arthroplasty (group C). The participating surgeons have large experience in all three techniques. A standardized Case Record Form (CRF) will register the surgeon's findings and this CRF, together with the randomisation envelope, will be returned to the data center in a sealed envelope.

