### (C) Anterior cervical discectomy with disc prosthesis (ACDP)

The device used in the present trial is the Activ-C Flat artificial disc (B. Braun Aesculap, Germany)[20]. After the standard anterior discectomy is performed, the implant size will be determined and the endplates will be prepared for proper fitting of the prosthesis. The device will be inserted under slight distraction and fluoroscopic guidance. Whenever, for surgical-technical reasons, it is not possible to implant the disc prosthesis, an interbody fusion will be performed. Whenever this is impossible as well, only discectomy will be performed.

All patients will be encouraged to mobilise as soon as possible without a collar. Hospital admission will be 1-3 days, depending on the usual care of the participating hospital. Patients are stimulated to resume home activities and work as soon as possible.

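### After surgery, complications are first scheduled for assessment at week 8, although patients go home after 1-3 days and are already sent questionnaires at weeks 2 and 4

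*Protocol article*

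**What the plan says.** Under "3) Complications" the protocol article plans "A systematic assessment of complications (including wound infection, deep venous thrombosis, urine tract infection, haematoma, progressive neurological deficit, dysphagia, and hoarseness", which "will be carried out by the surgeon and research nurse". It adds: "Surgeons will also document perioperative complications like cerebrospinal fluid leakage, vascular injury, nerve root damage, and malposition of the implant". Under Intervention, "A standardized Case Record Form (CRF) will register the surgeon's findings".

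The timing is in Outcome assessment and Table 2. For clinic visits: "Follow-up examination will take place at 8, 26, 52, 104 and 260 weeks after randomisation". For postal contacts: "At 2, 4, 12, 156 and 208 weeks after randomisation, questionnaires will be sent by mail". The Complications row of Table 2 is marked at surgery and at 8, 52, 104, 156, 208 and 260 weeks. It is blank at 2, 4, 12 and 26 weeks.

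On hospital stay, the text after the description of the third technique says: "Hospital admission will be 1-3 days, depending on the usual care of the participating hospital". The Randomisation procedure section keeps patients and research nurses blinded for 2 years.

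**The concern.** The list of complications to be assessed systematically includes events that belong largely to the early post-operative period. That is clinical background and not a statement of the article. It fits dysphagia and hoarseness best and progressive neurological deficit poorly. The schedule leaves the weeks after discharge uncovered, although the trial writes to every patient twice in that time.

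A patient whose swallowing or voice trouble came and went without treatment is counted only if it is remembered at week 8. The Discussion presents the trial as a test of the safety of the prosthesis as well as its effect, and calls for the discectomy-only arm to justify the cost of implants. If transient harms differ between arms with and without an implant, under-counting them everywhere makes the absolute difference look smaller than it is.

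**Working it through.** The plan states no figure to reproduce here. The main check is a reading of the schedule.

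**Step 1. Table 2, column by column.**

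| Row | Surgery | 2 wk | 4 wk | 8 wk | 12 wk | 26 wk | 52 wk |
|---|---|---|---|---|---|---|---|
| Visit number | 4 | – | – | 5 | – | 6 | 7 |
| Complications | X | – | – | X | – | – | X |
| Neurological examination | – | – | – | X | – | – | X |
| NDI | – | X | X | X | X | X | X |
| Cost diaries | – | – | – | – | X | X | X |

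The NDI row confirms contact at weeks 2 and 4. The other instruments marked at those weeks are McGill, VAS arm and neck, SF-36, Karasek, Likert and EuroQol. None is described in the article as a record of complications.

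**Step 2. Length of the gap.** Follow-up is counted from randomisation, which takes place in the operating room, so week 8 is 8 × 7 = 56 days after surgery. With 1-3 days in hospital, the uncovered time at home is 56 − 3 = 53 to 56 − 1 = 55 days.

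**Step 3. What other sources cover.**
- The mark at surgery, the operative form and the surgeon's perioperative record cover findings at operation.
- The week-8 neurological examination would find a deficit that persists, but not swallowing or voice trouble that has resolved.
- The cost diaries (section on Costs) record care used, medication and expenses, so a treated event may appear there. Untreated dysphagia or hoarseness would not be expected to.

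The residue is short-lived, untreated events after discharge.

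**Step 4. Effect of equal under-counting (illustration only).** The event rates and the fraction missed are assumptions. Group size is 750 / 3 = 250, from the Sample size section. If a fraction m of true events is missed in both arms and no false events are added, each rate is multiplied by (1 − m). The risk difference is then multiplied by (1 − m), and the risk ratio does not change. Approximate power at two-sided 0.05 is Φ(|p1 − p2| / SE − 1.96), with SE = √[(p1(1 − p1) + p2(1 − p2)) / 250].

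| m | Rates seen | Risk difference | Risk ratio | SE | Power |
|---|---|---|---|---|---|
| 0 | 20% v 10% | 10.0 points | 2.0 | 0.0316 | Φ(1.20) ≈ 88.5% |
| 0.25 | 15% v 7.5% | 7.5 points | 2.0 | 0.0281 | Φ(0.71) ≈ 76% |
| 0.50 | 10% v 5% | 5.0 points | 2.0 | 0.0235 | Φ(0.17) ≈ 57% |

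The table shows direction and mechanism. It does not estimate what this trial would lose, and the article sets out no specific test of complications.

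**The case against.** The strongest reply is that the schedule is coherent. The surgeon and research nurse assess complications, weeks 2 and 4 are postal, and so no clinician assessment is marked there. A journal article also leaves form content and reporting between visits to the full protocol.

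This does not remove the point. The timing of the assessment is printed in Table 2, so it is a stated choice and not an omitted detail. Nor is a postal week treated as unable to carry the mark: Table 2 marks Complications at weeks 156 and 208, which the text lists as mail contacts. That comparison is not perfectly clean, because Table 2 also marks a neurological examination and dynamic X-ray at those weeks.

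Other parts of the reply stand:
- Complications are an ancillary outcome here, listed under Other outcome measures. The primary comparison, its power and its error control are untouched.
- Infection, thrombosis or haematoma that needed treatment would probably leave a clinical record. This is an assumption, since the article does not name the data source.
- Equal under-counting leaves the risk ratio unchanged; only absolute differences and precision suffer.

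A reader might also infer three stronger things that the document does not support. One is that nothing about complications is recorded before week 8; the mark at surgery and the surgeon's record contradict that. Another is that most early complications rest on recall. The article gives no durations, so any such percentage would come from assumed ones, and would apply to only two of the seven listed complications. The third is that the unblinded surgeon biases the count between arms. The surgeon does know the allocation and is a named assessor, but differential reporting is not shown, and patients and nurses are blinded through the period in question.

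**Conclusion.** The point holds in a limited form. No complication assessment is scheduled between surgery and week 8, which leaves 53 to 55 days at home uncovered despite two existing contacts. The events affected are short-lived and untreated ones after discharge, chiefly dysphagia and hoarseness. These are probably under-counted in all arms, which shrinks absolute differences between the implant arms and discectomy alone.

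The size of the loss cannot be derived from the document. The conclusion assumes that some of these events resolve before week 8 without treatment, that some are then forgotten, and that forgetting is similar across arms because patients and nurses are blinded. This is a cheap improvement to an ancillary safety outcome and not a flaw in the main comparison.

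**What to change.** Mark Complications at weeks 2 and 4 in Table 2. Add a short fixed block to the questionnaires mailed at those weeks:
- swallowing difficulty
- hoarseness
- wound problem
- treatment for infection or thrombosis
- new weakness or numbness
- unplanned care

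Each item is answered yes or no, with the date and whether it is still present.

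Name these blinded patient answers as the main source for dysphagia and hoarseness after discharge. Keep the surgeon and nurse assessment for all other complications. Restricting the surgeon's record to perioperative events could lose surgeon-diagnosed events that arise after discharge.

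The cost is an amendment to Table 2, a few items on two forms already sent, and slight extra burden for patients. No extra visit is needed. Recorded complication rates will rise because more events are asked about, and the report should say so when it is compared with trials that did not ask.

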## Methods/Design

We designed an observer and patient blinded randomised cost-effectiveness trial in the treatment of cervical disc herniation in which three surgical techniques are compared in a parallel group design. Adjacent level disease will be used as primary outcome measure and NDI as secondary outcome. As such we will evaluate the clinical appropriateness and superiority of disc prosthesis on one hand, cervical fusion on the other hand, and compare this to discectomy without any implant. The follow-up period will last 5 years.

In order to collect enough patients, a multicenter design is necessary. The clinical centers that are planned to recruit patients into the NECK trial are: Medical Center Haaglanden, The Hague; Leiden University Medical Center; University Medical Center Groningen; Medical Center Alkmaar; and University Medical Center Maastricht. The protocol was approved by the ethics committee/IRB in each participating hospital.

The primary question of the NECK trial is whether ACDP has a lower incidence of symptomatic adjacent disc degeneration compared to ACD and ACDF. Symptomatic adjacent level disease is defined as development of new symptoms (i.e. neck pain, radiculopathy, or myelopathy) referable to a motion segment adjacent to the site of the previous anterior surgery. In addition, we want to identify certain subgroups that may benefit more of one of the allocated treatments.

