### Randomisation procedure

Patients will be randomly allocated to ACD, ACDF, or ACDP. Randomisation will take place on the operating room within 6 weeks after the first visit to the research nurse. A randomisation list is prepared for every participating hospital-nurse combination. Variable sized blocks of random numbers are formed to ensure equal distribution of the randomisation treatments over hospitals and research nurses. The data manager, who is not involved in the selection and allocation of patients, will prepare coded, sealed envelopes containing the treatment allocation. In the operating room, after induction of anaesthesia, the surgeon will open the envelope and the allocated treatment will be performed. Patients and research nurses will be kept blinded for the allocated treatment for 2 years.

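### Judgement-based complications are rated by both the unblinded surgeon and the blinded nurse, and the blinded rating is given no precedence, so this comparison is not fully observer-blind

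*Protocol article*

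**What the plan says.** All references are to the protocol article.

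- **Methods/Design** sets the level of blinding: "We designed an observer and patient blinded randomised cost-effectiveness trial".
- **Randomisation procedure** shows who learns the arm: "In the operating room, after induction of anaesthesia, the surgeon will open the envelope and the allocated treatment will be performed". It then names those kept unaware: "Patients and research nurses will be kept blinded for the allocated treatment for 2 years". Surgeons are not among them.
- **Intervention** protects the theatre record. The surgeon's case record form, "together with the randomisation envelope, will be returned to the data center in a sealed envelope".
- **Complications** (under Other outcome measures) assigns the systematic assessment to two people: "progressive neurological deficit, dysphagia, and hoarseness) will be carried out by the surgeon and research nurse". A separate sentence adds the theatre events: "Surgeons will also document perioperative complications like cerebrospinal fluid leakage, vascular injury, nerve root damage, and malposition of the implant".
- **Table 2** schedules complications at surgery and at 8, 52, 104, 156, 208 and 260 weeks. It does not say which assessor acts at which time.

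**The concern.** Some of the listed complications, such as dysphagia, hoarseness and progressive neurological deficit, depend on how the patient is questioned and on the assessor's judgement. If a person who knows the arm rates them, recording may differ between arms even when the true rates do not. The protocol itself treats preference as relevant, since the surgeon's treatment preference is recorded at baseline. The Discussion says that the trial is meant to show both the effectiveness and the safety of the prosthesis, so the harm comparison is part of the stated purpose although complications are not a primary or secondary outcome.

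There is a secondary worry. Surgeon and nurse share one task, and no separation between them is described, so the arm could become known to the nurse.

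**Working it through.** The article gives no figure to reproduce on this point. The check sets the statements side by side.

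1. **Does the surgeon know the arm?** Yes. The surgeon opens the envelope and operates, and is not listed as blinded. That the surgeon in the Complications section is the operating surgeon is the natural reading, though it is not stated.
2. **Is the surgeon's role limited to theatre events?** The text does not limit it. The perioperative events come in a separate sentence, worded as an addition to the systematic assessment. The surgeon is therefore named for the post-operative list as well.
3. **Is there a blinded assessor?** Yes. The research nurse is named in the same sentence and is blinded for 2 years, that is, to 104 weeks. In Table 2 that covers the complication records at 8, 52 and 104 weeks. Those at 156, 208 and 260 weeks fall after the blind ends.
4. **Whose rating is compared between arms?** Not stated. The sentence describes one assessment by two people. If a blinded and an unblinded rating are merged, the result is not a blinded comparison.
5. **Is a leak to the nurse documented?** No. The article does not say that the two assess together, share a form or exchange information, and the theatre form goes sealed to the data centre.

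**Illustration of sensitivity (assumed inputs).** The planned totals give 675/3 = 225 per arm before, and 750/3 = 250 per arm after, the allowance for loss to follow-up. Assume the same true rate p in both arms, complete recording in one arm and a share c recorded in the other. The spurious difference is d = p − pc. The chance of a two-sided p < 0.05 is approximately Φ((d − 1.96·s0)/s1). Here s0 = √(2m(1−m)/n), m is the mean of p and pc, and s1 = √([p(1−p) + pc(1−pc)]/n).

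For p = 15%, c = 70%, n = 225:
- pc = 10.5%, d = 4.5 points, m = 12.75%
- s0 = 0.03145 and s1 = 0.03137
- (0.045 − 1.96 × 0.03145)/0.03137 = −0.53, so the chance is about 0.30

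| True rate | Share recorded in one arm | Spurious difference | Chance of p < 0.05, n = 225 | n = 250 |
|---|---|---|---|---|
| 5% | 80% | 1.0 point | 0.074 | 0.078 |
| 10% | 70% | 3.0 points | 0.206 | 0.224 |
| 15% | 70% | 4.5 points | 0.298 | 0.325 |
| 20% | 70% | 6.0 points | 0.395 | 0.431 |

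The formula counts the tail in the direction of the bias. Adding the other tail raises the first row to about 0.08 and leaves the rest almost unchanged. The nominal level is 0.05. Neither p nor c comes from the article. The table also takes the biased record as the only one, whereas a blinded nurse records too.

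**The case against.** The case on the other side has real weight.

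- **A blinded assessor is already assigned.** A reader might infer that harms are rated by the surgeon alone and that the comparison is simply unblinded. The text does not support that, because the nurse is named alongside the surgeon. This stands, and it limits the point to *not fully* observer-blind.
- **The blinding label need not cover surgeons.** The article spells out that patients and nurses are the blinded parties. That softens the conflict with Methods/Design but does not remove it, because the surgeon is made an observer of this outcome.
- **A leak to the nurse, and through her to the primary outcome, is inference.** A reader might see a breach in the shared task. None is described, the theatre form is sealed, and who fills in which form may be set out in the full protocol. Nor does the article name the nurse as assessor of the symptomatic part of the primary outcome. The scales for symptoms are completed by patients, who are themselves blinded. A leak can be called a possible risk and no more.
- **The bias may have no single direction.** The Discussion describes divided habits, with fusion in most general hospitals and discectomy alone among most academic surgeons. Opposed preferences would partly cancel. This stands, and it is one reason why the figures above are not predictions.
- **Two sources of ascertainment are defensible for safety.** The first follow-up examination is at 8 weeks, and the contacts at 2 and 4 weeks are mailed questionnaires. A nurse-only checklist would miss early events or rely on recall for them. This stands and shapes the fix.
- **Complications are a lesser outcome.** They do not enter the sample size or the stopping rules, and most listed items are fairly objective. This bears on the priority of the point rather than on whether it is correct.

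Recording of theatre events such as cerebrospinal fluid leakage by the unblinded surgeon is unavoidable and is not criticised.

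**Conclusion.** The point holds in a limited form. The article assigns post-operative complications, including judgement-based items, to one assessor who knows the arm and one who does not, and it does not say that the blinded rating takes precedence. The between-arm comparison of those items is therefore not fully observer-blind, despite the general description of the trial.

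The conclusion rests on the natural reading that the assessing surgeon is the operating surgeon. Its numerical size is unknown. The range of about 7% to 43% for a spurious significant result depends wholly on the assumed true rates of 5% to 20% and one-arm recording of 70% to 80%, with no correction from the nurse's record. The definition of the primary outcome and the sample size are not affected. This is an inexpensive improvement, not a fault that threatens the trial.

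**What to change.** Amend the Complications section as follows.

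1. State that the surgeon and the research nurse record complications independently, on separate forms.
2. State that the surgeon's form goes directly to the data centre, as the Intervention section already arranges for the theatre form, and not through the nurse.
3. For dysphagia, hoarseness and progressive neurological deficit, make the blinded nurse's record, taken from the patient at the planned visits up to 104 weeks, the one compared between arms.
4. Keep surgeon-recorded perioperative, early and objective events (for example haematoma, wound infection and thrombosis) in the complication report, labelled as unblinded. No safety information is lost.

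**Cost.** A few sentences of protocol text and a change of form layout, with no new staff or visits. Two limits remain. Subjective symptoms that resolve before the 8-week visit will rest on patient recall in the blinded comparison, and ratings after 2 years are not blinded.
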